| Background | One in three Medicare enrollees received their insurance beneﬁts through Medicare Advantage (MA) plan.^1^ After the passage of the Medicare Modernization Act, there has been a rapid increase in MA enrollment and use of skilled nursing facilities (SNF) for post-acute rehabilitation services compared to inpatient rehabilitation facilities. Previous studies examining utilization of rehabilitation services and the quality of care have focused on Medicare fee-for-service (FFS) patients.^2^ However, there is no information about the rehabilitation quantity, quality, and outcomes of care among MA patients staying in SNF. The Office of Inspector General reported that SNFs upcode the FFS patients into higher payment RUGs categories, leading to more hours of therapy without a substantial rise in case-mix (age and diagnoses at admission were largely unchanged from 2006 to 2008).^3^ It is unknown whether this inappropriate selection of higher paying RUG therapy group in SNFs is affecting MA patients or not and how it influences the clinical outcome in these two groups. Our group has recently published a paper about rehabilitation service utilization in patients with hip fracture among Medicare FFS beneficiaries.^2^ Jung et al. reported that there is an increase in the quantity of therapy among FFS patients with hip fracture without change in case mix at SNF admission.^2^ [name] is interested in extending this research in the MA population and comparing this with traditional FFS patients. Initially, we thought of using MDS-3 assessment completed on all Medicare- or Medicaid-certified nursing home residents irrespective of their insurance status. However, after doing a comprehensive literature review, we found that hospitals receiving a disproportionate share and educational training payments and supplements submit claims for MA beneficiaries.^4^ Therefore, we decided to use inpatient claims and HEEDIS for retrieving hospital related information. |

| **Data Sources** | **Variables** | **Link** | **Years** |
| --- | --- | --- | --- |
| Medicare Provider and Analysis Review (MedPAR) | Types of Fracture, Hospital length of stay, ICU, HCC score, hospital acquired conditions, and fracture management using ICD-9 procedure codes. | <https://www.resdac.org/cms-data/files/medpar-rif> | 2010-2015  Year 2010 was used to look back |

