| **Inclusion Criteria** | **Dataset: MedPAR Year:** January 2010 (lookback period for 2011) through June 2015  Patients admitted to hospital with hip fracture  MS-DRG codes: 533, 534, 535, and 536  Primary ICD-9-CM diagnostic codes: 82000, 82021, 82022, 82023, 82024, 82026, 82027, 82028, 82029, 82030, 82031, 82032, 8208, 82080, 82009, and 8080  Age ≥ 65 years  Patients from hospital with no information on disproportionate share  Length of stay less than 15 days  Discharged to only SNF  Admitted to SNF within 3 days of discharge from hospital  Merge with American community Survey  Exclude previous nursing home stay in past twelve months  Exclude previous hospitalization in past twelve months  **Dataset: MDS-3** - **Inclusion Criteria**  First-time SNF admissions from acute care hospitals identified on the basis of the presence of an MDS admission assessment tracking record  Include short term and long-term stay  Patients must have at least two assessments.  Patients must have first MDS assessment within 10 days of admission to SNF  Patients must have at least second or subsequent MDS (last) assessment within 10 days of discharge from SNF or any assessment.  Exclude Patients in coma  Exclude patients’ with any missing information on variables  Exclude patients’ with extreme therapy minutes and outliers  Exclude patients’ from Hawaii, Virgin Island, and Puerto Rico  Since 2008, the MedPAR file contains claims information on MA enrollees receiving care in disproportionate share hospitals (DSH) and Indirect Medical Education or Direct Medical Education adjustments. Therefore, our study cohort will be limited to patients discharged from these hospitals. |

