**Original Statistical Analysis**

There are some evidence showing cherry picking of healthier beneficiaries in MA plans and sicker patients switching from MA to FFS. There might be a level of endogeneity in the selection of MA enrollees. We anticipated that MA and FFS beneficiaries might differ with respect to demographic, clinical, and socioeconomic characteristics. To account for differences in observed demographic and clinical characteristics between FFS and MA, we will generate a propensity score that will reflect the probability of individuals to be in MA versus FFS program using observable baseline characteristics. Propensity score model will include age, gender, race, marital status, length of stay in the hospital, number of days in the intensive care unit, fracture treatment, number of comorbidities, admission cognition, body mass index, hospital-acquired complications, HCC score, dual Medicare/Medicaid status, median household income, household education and state fixed effects. After that, Inverse Probability of Treatment Weighs (IPTW) will be generated from the propensity scores to balance the differences in patient demographic and clinical characteristics.

We will compare baseline characteristics between FFS and MA using chi-square tests for categorical variables and t-tests for continuous variables then weights were applied to calculate weighted rates and mean. First, we will use linear probability model without applying IPTW to compare the difference in outcomes between MA and FFS and then we will use IPTW.

After that, we will use a linear probability model to compare outcomes between FFS and MA patients after applying IPTW and SNF fixed-effect.

**After reviewer feedback:** We added odds ratio from logistic regression models to compare the binary outcome variables for 30-day hospital readmission, becoming a long-stay resident and successful discharge to the community.

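### Admission year is missing from the propensity score list and is named in no outcome model or table, so time trends may confound the MA versus FFS comparison

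*Protocol*

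**What the plan says.** The Inclusion Criteria give the MedPAR period as "January 2010 (lookback period for 2011) through June 2015". With 2010 used only to look back, index admissions span about 4.5 years and are analysed as one cohort.

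Original Statistical Analysis lists the propensity score covariates one by one. The list begins "Propensity score model will include age, gender, race, marital status, length of stay in the hospital, number of days in the intensive care unit" and ends "median household income, household education and state fixed effects". No year, quarter or date of admission is on it. The same section names the outcome models: a linear probability model without weights, the same model with IPTW, and one with IPTW and an SNF fixed effect. Logistic models for the binary outcomes were added later. None mentions calendar time. The Table 1 shell has no row for admission year, and Tables 2 and 3 have no year-adjusted column.

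The Background says that after the Medicare Modernization Act "there has been a rapid increase in MA enrollment and use of skilled nursing facilities (SNF) for post-acute rehabilitation services". It also cites an earlier study by the same group, which found that "there is an increase in the quantity of therapy among FFS patients with hip fracture without change in case mix at SNF admission".

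**The concern.** A variable confounds this comparison if it is linked both to plan type and to the outcome. The protocol's own background suggests both links for calendar time: MA membership was growing, and so was therapy quantity, which is a main outcome in Table 2. The therapy increase came without a change in case mix. Patient covariates such as HCC score, cognition and fracture treatment therefore cannot be relied on to stand in for time.

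Weighting balances only what enters the score. State fixed effects in the score, and SNF fixed effects in the last model, remove stable differences between places. They do not remove a change over the years within a state or a facility. If the trends continued, part of a general drift in practice would be attributed to plan type, and Table 1 as laid out would not show the imbalance.

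**Working it through.** The plan states no figure on this point, so there is none to reproduce. The check sizes the possible bias under assumptions.

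**Inputs**
- From the protocol: window T = 4.5 years (January 2011 to June 2015).
- Assumed: uniform accrual; a linear rise in MA share from p0 to p1; the same linear outcome trend in both groups; other covariates unrelated to admission date. The protocol gives no yearly MA share and no annual trend for any outcome.

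**Gap in mean admission date, MA minus FFS**

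With p = (p0 + p1)/2 and slope = (p1 − p0)/T:

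gap = slope × (T²/12) / [p(1 − p)], where T²/12 = 20.25/12 = 1.6875.

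| Assumed MA share | slope × 1.6875 | p(1 − p) | gap (years) |
|---|---|---|---|
| flat at 25% | 0 | 0.1875 | 0 |
| 25% to 30% | 0.01875 | 0.1994 | 0.09 |
| 20% to 30% | 0.0375 | 0.1875 | 0.20 |
| 20% to 35% | 0.05625 | 0.1994 | 0.28 |
| 20% to 40% | 0.075 | 0.2100 | 0.36 |
| 15% to 40% | 0.09375 | 0.1994 | 0.47 |

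**Bias in the MA minus FFS difference = gap × annual outcome trend**
- At an assumed 3% of the mean per year: 0.09 × 3% ≈ 0.3% of the mean for the smallest non-zero gap, 0.20 × 3% = 0.6%, and 0.47 × 3% ≈ 1.4% for the largest.
- Over assumed trends of 1% to 10% per year and all non-zero gaps: about 0.1% to 4.7% of the mean. The upper end needs both a 15% to 40% rise in share and a 10% annual trend.
- In absolute terms, with an assumed 50 minutes per year: 0.20 × 50 = 10 minutes and 0.357 × 50 ≈ 18 minutes. The protocol gives no mean therapy minutes against which to judge these.

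**Does IPTW without calendar time leave this bias in place?** One million patients were simulated with a true MA effect of zero. The MA share was about 22% in the first year and 29% in the last. The outcome rose by 3 units per year from a starting mean of 100, and one patient covariate affected both plan type and outcome. IPTW on the patient covariate alone gave a spurious difference of +0.57 units, about 0.6% of the starting mean. With admission time added to the score the difference was −0.03, zero within simulation error.

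**Direction.** If therapy and MA share both rise, later admission raises MA relative to FFS. The Working Hypothesis is that FFS patients receive more therapy, so this bias would shrink the hypothesised difference.

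**The case against.** The strongest objection is that the background does not establish either trend for this cohort. The growth in MA enrolment is dated only as after the Act, with no yearly shares. The one dated period belongs to the upcoding report, whose statement that "age and diagnoses at admission were largely unchanged from 2006 to 2008" precedes the study window. The hip-fracture therapy increase is given without years or rate, and for FFS patients only. The cohort is also restricted to hospitals with disproportionate-share or medical-education adjustments, and nothing shows how the MA share moved there. All of this stands. A reader might infer that time trends do confound the comparison, or that MA patients are in fact admitted later. The documents support only a risk, and with a flat MA share the bias is zero.

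A second objection is that the documents report no trend for length of stay, ADL change, readmission, long stay or community discharge. That is correct. Any figure for those outcomes would rest wholly on assumption, and the direction there is unknown.

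A third is that the outcome models are described without a covariate list, and a full specification may sit in an analysis plan that is not shown. This weakens the point for the outcome models. It does not touch the propensity score, whose covariates the protocol lists down to the choice of fixed effects.

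**Conclusion.** The point holds as a gap in the stated adjustment, not as a demonstrated bias. The propensity score list omits calendar time in a cohort pooled over about 4.5 years, although the protocol's own background gives reason to expect time to be related to plan type and to therapy quantity. State and SNF fixed effects do not close the gap.

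The size cannot be obtained from the documents. Under assumed rises in MA share of 20% to 30% or 20% to 40%, the admission-date gap is 0.20 or 0.36 years. At an assumed 3% annual trend the bias is then about 0.6% or 1.1% of the mean (0.357 × 3%), which is modest.

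A reader might also infer that the omission could produce the hypothesised FFS excess in therapy. It could not do so through the trends the background describes, because rising therapy with a rising MA share pushes the other way. A bias that understates the difference is still worth removing when the remedy is this simple. This is a recommended improvement and does not by itself invalidate the comparison.

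**What to change.** Add indicators for year of index admission to the propensity score model and to the IPTW and IPTW plus SNF fixed-effect regressions. Quarter indicators would serve as well. State the term explicitly for the outcome models, including the weighted logistic models. Add admission year to Table 1, before and after weighting, so that readers can see whether plan type shifted over time and whether the weights balanced it.

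Five calendar years need four indicators; the 18 quarters would need 17. No new data are required, because admission dates are already used to select the cohort and to compute SNF length of stay. The protocol states no sample size, so the effect on precision cannot be worked out from it; the visible cost is a few extra model terms. If the MA share or the outcomes were flat over time, the estimates should barely move.

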**Recommended Tables**

**Table 1.** Characteristics of Medicare Fee-For-Service versus Medicare Advantage Patients with Hip Fracture before and after Inverse Probability of Treatment Weighting.

| **Variables** | **Unadjusted** | | **IPTW-adjusted** | |
| --- | --- | --- | --- | --- |
|  | FFS | MA | FFS | MA |
| Age |  |  |  |  |
| Female |  |  |  |  |
| Married |  |  |  |  |
| Race | | | | |
| White |  |  |  |  |
| Black |  |  |  |  |
| Hispanic |  |  |  |  |
| Others |  |  |  |  |
| Dual |  |  |  |  |
| Safety-net Hospitals % |  |  |  |  |
| Hospital Length of Stay |  |  |  |  |
| Intensive Care Length of Stay |  |  |  |  |
| HCC Score (Comorbidity Index) |  |  |  |  |
| Hospital Acquired Conditions % |  |  |  |  |
| **Fracture Treatment** | | | | |
| Open Reduction Internal Fixation |  |  |  |  |
| Close Reduction Internal Fixation |  |  |  |  |
| Internal Fixation |  |  |  |  |
| Partial Hip Replacement |  |  |  |  |
| Total Hip Replacement |  |  |  |  |
| Non-Surgical Management |  |  |  |  |
| Body Mass Index |  |  |  |  |
| Admission ADL |  |  |  |  |
| Admission Pain Status |  |  |  |  |
| **Cognition** | | | | |
| Intact |  |  |  |  |
| Mild Impairment |  |  |  |  |
| Moderate Impairment |  |  |  |  |
| Severe Impairment |  |  |  |  |
| **SNF Characteristics % and Staffing (mean ± SD)** | | | | |
| For Profit |  |  |  |  |
| Part of Chain |  |  |  |  |
| Total RN/LPN FTE |  |  |  |  |
| Total PT- FTE |  |  |  |  |
| Total OT-FTE |  |  |  |  |
| Total MD-FTE |  |  |  |  |

Cognition categories: Measured by the Cognitive Function Scale (CFS) using Cognitive Performance Scale (CPS) and Brief Interview for Mental Status (BIMS) from MDS admission assessment. Pain categories: If patient is having pain that affects sleep and functional activity in last 5 days Admission ADL score ranges from 0 - 28 (higher scores indicate more impairment). Full-time equivalent (FTE): 35 hours’/ week work in the SNF as a staff or on contract.

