**Abbreviation:** FFS- Fee-for-Service; MA- Medicare Advantage; SNF- Skilled Nursing Facilities; HCC- Hierarchical Condition Category; ADL- Activities of Daily Living; SD- Standard Deviation; IPTW- Inverse Probability of Treatment Weighting; FTE- Full-Time Equivalent; Total RN/LPN FTE- Total number of full-time equivalent Registered Nurse and Licensed Practical Nurse; Total PT- FTE- Total number of full-time equivalent Physical Therapist; Total OT- FTE- Total number of full-time equivalent Occupational Therapist; Total MD- FTE- Total number of Full-time Physician.

**p<0.01, *p<0.05

**Table 2**: Length of Stay and Amount of Rehabilitation Care in Medicare Fee-For-Service versus Medicare Advantage Patients

|  | **Unadjusted** | | | **Adjusted** | |
| --- | --- | --- | --- | --- | --- |
|  | FFS | MA | Differences based on linear probability model  (95% CI)  [p-value] | Differences after IPTW-Adjusted based on linear probability model  (95% CI)  [p-value] | Differences after IPTW-Adjusted SNF Fixed Effect (95% CI)  [p-value] |
| SNF Length of Stay  Mean (SD) [median] |  |  |  |  |  |
| Rehabilitation Therapy (Minutes) Mean (SD) [median] | | | | | |
| Total Physical Therapy |  |  |  |  |  |
| Total Occupational Therapy |  |  |  |  |  |
| Total Rehabilitation Therapy |  |  |  |  |  |
| Rehabilitation Therapy/Day |  |  |  |  |  |

**Note:** SNF Length of Stay: follow-up to 180 days. Total Therapy: Sum of therapy minutes (Independent + Concurrent + Group) administered to the resident up to 40 days. Total Rehabilitation Therapy: Combined Occupational therapy + Physical therapy minutes. Rehabilitation Therapy/day: Total Rehabilitation therapy divided by length of stay up to 40 days.

**Table 3:** Patients Outcomes in Medicare Fee-For-Service versus Medicare Advantage Patients before and after Inverse Probability of Treatment Weighting and SNF Fixed Effect.

|  | **Unadjusted** | | | | **Adjusted** | | |
| --- | --- | --- | --- | --- | --- | --- | --- |
|  | FFS | MA | Differences based on linear probability model  (95% CI)  [p-value] | *Odds Ratio based on logit model  (95% CI)  [p-value] | Differences after IPTW Adjusted  based on linear probability model  (95% CI)  [p-value] | *Odds Ratio based on logit model  (95% CI)  [p-value] | Differences after IPTW-Adjusted SNF Fixed Effect  [p-value] |
| Change in ADL |  |  |  |  |  |  |  |
| 30-Day Hospital Readmission % |  |  |  |  |  |  |  |
| Became Long-Stay Resident % |  |  |  |  |  |  |  |

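### Baseline comparison is fixed as chi-square and t-tests with p-value stars; the weighted columns of Table 1 have no size-based balance measure and no step that acts on residual imbalance

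*Protocol*

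**What the plan says.** The section Original Statistical Analysis generates inverse probability of treatment weights from a propensity score "to balance the differences in patient demographic and clinical characteristics". It then says that baseline characteristics will be compared "using chi-square tests for categorical variables and t-tests for continuous variables then weights were applied to calculate weighted rates and mean". By the order of that sentence the tests come before the weighting, and after weighting only rates and means are named.

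Under Recommended Tables, Table 1 is titled "Characteristics of Medicare Fee-For-Service versus Medicare Advantage Patients with Hip Fracture before and after Inverse Probability of Treatment Weighting". It has FFS and MA columns in an unadjusted block and again in an IPTW-adjusted block. It has no difference column. A star key, "p<0.01, *p<0.05", stands below its abbreviations and does not say which columns the stars mark.

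The propensity model's covariate list ends with "median household income, household education and state fixed effects". None of these three has a row in Table 1. Conversely, admission ADL, admission pain status and safety-net hospital have rows in Table 1 but are not in the propensity list.

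**The concern.** The weighted comparisons in Tables 2 and 3 are credible only as far as the weights have made the two payer groups alike on measured characteristics. The protocol itself expects selection: healthier people entering MA and sicker people moving to FFS. Whether weighting dealt with this is a question about the size of the remaining differences. A chi-square or t-test answers another question, namely whether a difference can be told apart from zero at the available sample size. In a multi-year Medicare cohort, stars may therefore mark negligible and important differences alike.

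The three Table 1 characteristics outside the propensity model matter most. The weights are not built to balance them, so any balance on them is a by-product of balancing other covariates. Admission ADL is also the starting value of the change-in-ADL outcome, so residual imbalance there bears directly on a study result. The plan does not say what would happen if such an imbalance appeared.

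**Working it through.** **No figure to reproduce.** The protocol states no sample size, balance threshold or standardized difference. The check is therefore a reading of the text plus an illustration under assumed sizes.

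**1. Smallest difference that earns a star.** For a standardized difference d between groups of size n1 and n2, the test statistic is about z = d / sqrt(1/n1 + 1/n2). Two-sided p reaches 0.05 at d = 1.96 × sqrt(1/n1 + 1/n2).

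| Assumed FFS / MA | sqrt(1/n1 + 1/n2) | d at p = 0.05 |
| --- | --- | --- |
| 20,000 / 8,000 | 0.01323 | 0.026 |
| 50,000 / 20,000 | 0.00837 | 0.016 |
| 150,000 / 60,000 | 0.00483 | 0.009 |

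All three lie well below the conventional limit of 0.1, which is not taken from the protocol.

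**2. The same imbalance at different sample sizes.** The MA share of the cohort is not given. The Background says "One in three Medicare enrollees received their insurance" through MA, so a share of 0.25 to 0.33 is assumed.

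| Assumed total N | p for d = 0.02 | p for d = 0.10 |
| --- | --- | --- |
| 2,000 | 0.67 to 0.70 | 0.035 to 0.053 |
| 20,000 | 0.18 to 0.22 | below 1e-8 |
| 100,000 | 0.003 to 0.006 | effectively 0 |
| 200,000 | 0.00003 to 0.0001 | effectively 0 |

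Within each column the imbalance is constant, yet p runs from unremarkable or borderline to extreme. At N = 100,000 or more, differences of 0.02 and 0.10 would both carry two stars.

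**3. What the weighted columns already allow.** For a percentage row, d = (p1 − p2) / sqrt([p1(1 − p1) + p2(1 − p2)] / 2). Weighted values of 25% and 26% give 0.01 / 0.436 = 0.023; values of 50% and 55% give 0.05 / 0.499 = 0.100. A reader could thus work out the residual difference for binary and categorical rows. Continuous rows (age, BMI, HCC score, admission ADL, lengths of stay) also need a standard deviation, and the shell asks for one only in the SNF block.

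**4. Covariate list against table rows.**

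- In the propensity model without a Table 1 row: median household income, household education, state. Number of comorbidities has no separate row either, only the HCC score labelled as a comorbidity index.
- In Table 1 but not in the propensity model: safety-net hospital, admission ADL, admission pain status, and the SNF characteristics and staffing.

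**The case against.** The strongest reply is that Table 1 is itself a comparison after weighting: every listed row shows weighted FFS beside weighted MA, including the three that the weights do not target. That is correct. A reader might infer from the sentence on tests that the plan makes no comparison after weighting, or that Table 1 cannot reveal residual imbalance. The table's title and layout contradict both. Nor does the text say that balance will be judged by the p-values; it says only that characteristics are compared with those tests.

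A reader might also infer that ordinary tests will be run on the weighted sample, with apparent precision inflated by the weights. The protocol does not say so. The star key leaves its columns open, and neither the scaling of the weights nor the variance estimator is stated.

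It can further be said that stars on unweighted data alter no estimate, because the propensity covariates are listed in advance and the weights are applied regardless. That stands too. The harm lies in having no measure and no action rule after weighting, not in the stars themselves.

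Finally, the choice of balance measure is often left to a statistical analysis plan, which is not shown. This lowers the weight of the point but does not remove it. The protocol has its own statistical analysis section and table shells, and there it chooses significance tests and stars, a poor gauge of what the weights are meant to achieve.

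**Conclusion.** The point holds in a limited form. The only named tools for the baseline comparison are significance tests with p-value stars. Weighted means and rates will be shown, but without a size-based measure of the remaining difference and without a step that acts on it. Three Table 1 characteristics are not targeted by the weights, and three propensity covariates cannot be checked from Table 1 at all.

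The numerical size depends on sample sizes that the protocol does not give. Under the assumed range of 28,000 to 210,000 patients, standardized differences of 0.026 down to 0.009 would be starred. With about 2,000 patients the opposite weakness appears: a difference of 0.10 could miss significance (p up to 0.053).

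Nothing here shows that the weighted groups will in fact be imbalanced or that any estimate is biased. A balance table of any kind speaks only to measured covariates, so it could not show that all confounding had been removed. This is a cheap improvement.

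**What to change.** - In Table 1, drop the tests and the star key. Add two columns: the standardized difference before weighting and after weighting. Use the same denominator in both, such as the unweighted pooled standard deviation, and report standard deviations for continuous rows.
- Add rows for median household income, household education and state. For state, the largest absolute difference across states would be enough.
- State a limit in advance, for example an absolute weighted difference of 0.1 (a convention). Put any patient or hospital covariate above it into the propensity model or the weighted outcome model before effects are estimated. A covariate already in the propensity model would need a more flexible term there, or entry in the outcome model. Admission ADL, admission pain and safety-net status are the first to check.
- Keep the SNF rows descriptive. The rule is meant for patient and hospital covariates, and the plan already handles facility differences through SNF fixed effects.

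The cost is two columns, a few rows and possibly one refit of the weights, which may slightly widen the confidence intervals. No new data are needed, since all these variables are in the listed data sources. The Timeline places the weighted analysis in May 2017, so if estimates already exist, the balance columns can be computed from the existing cohort and any refit reported beside the planned result.

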**Timeline**:

| **Date** | **Proposed Activities** |
| --- | --- |
| November 2016 | First meeting to discuss research question- [name], a postdoc fellow, presented his research ideas and hypothesis in our regular research meeting. |
| December 2016 | Comphrensive literature review |
| January 2017 | Presented research strategy with literature review |
| February 2017 | Data retrieval and proposal drafted |
| February 2017 | Analytical cohort created |
| March 2017 | Descriptive Analysis completed |
| March 2017 | Discuss results with clinician and coauthors |
| April 2017 | Try to develop instrumental variable but could not able to find good one |
| April 2017 | Propensity Score Matching and then decided to use IPTW |
| May 2017 | Presented final analysis after using IPTW weights and SNF fixed effects |
| May 2017 | Present the results in Annual PO advisory board meeting |
| June 2017 | Sensitivity Analysis to compare long term risk: 6 moths and 1year mortality |
| July 2017 | First draft of manuscript including all tables and figures |

| **Study Retrieval Request** | |
| --- | --- |
| Data Requested | November 14 2016 |
| Analytical Cohort Completed | February 2017 |
| Unit of Analysis | Individual level |
| Research Questions | 1. Evaluate the differences in post-acute rehabilitation services utilization (physical therapy, occupational therapy) in older patients enrolled in Medicare health maintenance organizations (HMOs) and fee-for-service (FFS) systems during a short stay in skilled nursing facilities (SNFs). 2. Compare the differences in patients centered outcome associated with amount of rehabilitation services utilization during a short stay in skilled nursing facilities (SNFs). |
| Working Hypothesis | FFS patients will be receiving more rehabilitation therapy and staying longer in the SNF, and will have better outcomes. |
| Study Sample | We will select patients with a hip fracture for this study because this is an acute condition that commonly occurs in frail older adults and majority if them receives rehabilitation care in the SNF. |

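### The weights target payer balance overall and within states, but the SNF fixed-effect column compares payers within SNFs, so it can keep residual confounding that Table 1 would not reveal

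*Protocol*

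**What the plan says.** **Propensity model.** Under Original Statistical Analysis, the score is to give the "probability of individuals to be in MA versus FFS program using observable baseline characteristics". The covariates are listed one by one. They are demographic, hospital-stay and clinical items and dual eligibility, and the list ends with "median household income, household education and state fixed effects". No SNF indicator, SNF MA share or SNF case-mix mean appears.

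**Purpose of the weights.** "Inverse Probability of Treatment Weighs (IPTW) will be generated from the propensity scores to balance the differences in patient demographic and clinical characteristics".

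**Outcome models.** Three comparisons follow: unweighted, weighted, and weighted with SNF effects. For the third, "we will use a linear probability model to compare outcomes between FFS and MA patients after applying IPTW and SNF fixed-effect". No patient covariates are named as regressors.

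**Role of the result.** The third comparison fills the last column of Tables 2 and 3, "Differences after IPTW-Adjusted SNF Fixed Effect". The Timeline entry for May 2017 reads "Presented final analysis after using IPTW weights and SNF fixed effects".

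**Balance display.** Table 1 is titled "Characteristics of Medicare Fee-For-Service versus Medicare Advantage Patients with Hip Fracture before and after Inverse Probability of Treatment Weighting". It has FFS and MA columns for the whole cohort, unadjusted and weighted, and no within-SNF comparison.

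**The concern.** A propensity score that conditions on patient covariates and state removes the association between those covariates and payer over the whole cohort. If the model is correct, it also does so within each state. SNF fixed effects then discard every between-SNF contrast and use only differences between MA and FFS patients in the same facility.

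The covariate-payer association inside an SNF need not equal the one over the cohort or the state. The two part when SNFs in a state differ in MA share, and more so when MA share is related to case mix. Weights tuned to the overall association then under-correct or over-correct inside SNFs. The fixed effects remove facility-level differences, but not differences in patient mix between payers in one facility.

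The protocol itself expects patient-level selection: "cherry picking of healthier beneficiaries in MA plans and sicker patients switching from MA to FFS". The column at stake is the most adjusted one and the one the Timeline calls final. A reader who sees good weighted balance in Table 1 would naturally carry that assurance over to this column, where it does not apply.

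**Working it through.** The protocol states no figure on this point, so there is nothing of its own to reproduce. The mechanism was checked by simulation. **Every input below is an assumption.**

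**Set-up A**
- 1,500 SNFs of 20 patients and no state differences.
- One covariate x with SD 1: x = √0.25·m + √0.75·e, where m is the SNF component and e the patient component. So 25% of the variance lies between SNFs.
- logit P(MA) = -1.0 + 0.4·x + σ·u. Here u is an SNF effect with SD 1 and correlation ρ with m, and σ is the SD of SNF MA share on the logit scale. MA prevalence came out at about 28% to 31%.
- The propensity score is a logistic model in x without an SNF term. Weights are 1/p for MA and 1/(1-p) for FFS.
- Outcome slope: 5 percentage points per SD of x.

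**Quantities**
- Overall balance, as Table 1 would show it: weighted mean of x in MA minus that in FFS.
- Within-SNF balance: D = Σw·Ã·x̃ / Σw·Ã², where Ã and x̃ are payer and covariate minus their weighted SNF means.
- Bias of the SNF fixed-effect payer difference: 5 × D points.

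**Results (20 replicates per cell)**

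The overall weighted difference was 0.00 SD in every cell. The unweighted within-SNF difference was about 0.29 SD throughout. The weighted within-SNF difference D, in SD, was:

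| σ | ρ = -0.6 | -0.3 | 0 | 0.3 | 0.6 | Largest bias (points) |
|---|---|---|---|---|---|---|
| 0.25 | 0.08 | 0.05 | 0.03 | 0.00 | -0.02 | 5 × 0.078 = 0.39 |
| 0.5 | 0.13 | 0.09 | 0.04 | -0.01 | -0.06 | 5 × 0.135 = 0.67 |
| 1.0 | 0.23 | 0.15 | 0.06 | -0.02 | -0.11 | 5 × 0.235 = 1.17 |

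The sign changes with ρ. At σ = 1.0 the bias runs from about +1.2 to -0.6 points.

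**Set-up B, with state effects as the protocol specifies**
- 2,000 SNFs of 40 patients in 20 states, with state effects in the propensity model.
- 10% to 20% of the variance of x between SNFs.
- Log-odds of MA per unit x of 0 to -0.4 within SNFs and -1.2 to +1.6 between SNFs.
- SD of further SNF variation in MA share of 0 to 1.5, and the same outcome slope.

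The overall weighted difference was at most 0.005 SD. The within-SNF difference ranged in absolute value from 0.016 SD (no SNF variation in MA share beyond x) to 0.31 SD (between-SNF selection strongly opposed to within-SNF selection). The bias was therefore 0.08 to 1.56 points, in either direction. State effects do not remove the problem.

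**Effect of the remedy.** With x added as a regressor in the weighted SNF fixed-effect model, the bias was 0.00 points in every scenario of both set-ups, where the outcome was linear in x.

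**The case against.** - **The protocol does not exclude covariates from the final model.** True. It names none, and an analysis plan that is not shown could add them, which would largely remove the problem. A reader might infer that the model definitely carries no patient covariates, but the text does not go that far. It does list the propensity covariates one by one and then describes the outcome model by weights and SNF effects only, so the plain reading leaves the problem open.
- **The weights do more than balance payers overall.** This stands. State effects give balance within states if the model is right, and zip-level income and education may absorb some local variation. None of this reaches the SNF level.
- **The size is speculative.** This also stands. A reader might take 1.2 points as the expected bias. That value needs an SNF MA-share SD of about 1.0 on the logit scale together with the most extreme correlation tried. The protocol supplies neither.
- **Weighting still helps.** In Set-up A it reduced the within-SNF imbalance from about 0.29 SD in every cell, so the usual fault there is incomplete correction. It is not guaranteed: in Set-up B, where payer depended on x only between SNFs, weighting created a within-SNF imbalance of 0.08 to 0.14 SD.
- **Table 1 claims nothing about the last column.** Correct. It is an empty shell, and nothing says that it vouches for the SNF fixed-effect result. The point is only that it would not reveal the imbalance and that no other balance display is planned.
- **The columns stand side by side.** The IPTW-only column is unaffected, so a reader could see a divergence. The divergence would not show whether facility differences or residual patient mix caused it.

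**Conclusion.** The point holds as a limitation of one column, not as a failure of the weighting. As written, the IPTW plus SNF fixed-effect result in Tables 2 and 3 can keep within-SNF confounding of either sign, and the planned balance table would not show it.

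The document cannot give the size. With 25% of covariate variance between SNFs, MA log-odds of 0.4 per SD, 5 outcome points per SD and SNF-level correlations from -0.6 to 0.6, the largest bias is about 0.4, 0.7 and 1.2 points for SNF MA-share SDs of 0.25, 0.5 and 1.0. It is small if SNFs within a state have similar MA shares and case mix.

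The documents do not support a conclusion that the final estimates are biased by a known amount, or that the IPTW-only estimates share the problem. The change is worth making because the column is the one called final and the remedy is cheap.

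**What to change.** 1. In the IPTW plus SNF fixed-effect models for Tables 2 and 3, enter the propensity-score covariates as regressors and say so in the text. The state effects drop out, because each SNF lies in one state.
2. Beside Table 1, report weighted within-SNF balance: for each covariate, the payer coefficient from a weighted regression of that covariate on payer with SNF fixed effects, in SD units.

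The cost is a slightly larger regression and one more balance column, with no new data. The adjusted estimate then relies partly on the form in which the covariates enter the outcome regression. The 0.00-point result above assumed a linear outcome, so age, HCC score and hospital stay may need flexible terms. Adding SNF MA share and SNF covariate means to the propensity model is an alternative. In Set-up B it left at most 0.024 SD, or about 0.12 points.
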